# Personalising genetic counselling (POETIC) trial: Protocol for a hybrid type II effectiveness-implementation randomised clinical trial of a patient screening tool to improve patient empowerment after cancer genetic counselling

**DOI:** 10.1186/s13063-023-07723-0

**Published:** 2023-11-08

**Keywords:** Genetic counselling, Hybrid effectiveness-implementation trial, Patient screening tool, Randomised control trial

## Abstract

**Background:**

Genetic counselling aims to identify, and address, patient needs while facilitating informed decision-making about genetic testing and promoting empowerment and adaptation to genetic information. Increasing demand for cancer genetic testing and genetic counsellor workforce capacity limitations may impact the quality of genetic counselling provided. The use of a validated genetic-specific screening tool, the Genetic Psychosocial Risk Instrument (GPRI), may facilitate patient-centred genetic counselling. The aim of this study is to assess the effectiveness and implementation of using the GPRI in improving patient outcomes after genetic counselling and testing for an inherited cancer predisposition.

**Methods:**

The PersOnalising gEneTIc Counselling (POETIC) trial is a hybrid type 2 effectiveness-implementation trial using a randomised control trial to assess the effectiveness of the GPRI in improving patient empowerment (primary outcome), while also assessing implementation from the perspective of clinicians and the healthcare service. Patients referred for a cancer risk assessment to the conjoint clinical genetics service of two metropolitan hospitals in Victoria, Australia, who meet the eligibility criteria and consent to POETIC will be randomised to the usual care or intervention group. Those in the intervention group will complete the GPRI prior to their appointment with the screening results available for the clinicians’ use during the appointment. Appointment audio recordings, clinician-reported information about the appointment, patient-reported outcome measures, and clinical data will be used to examine the effectiveness of using the GPRI. Appointment audio recordings, health economic information, and structured interviews will be used to examine the implementation of the GPRI.

**Discussion:**

The POETIC trial takes a pragmatic approach by deploying the GPRI as an intervention in the routine clinical practice of a cancer-specific clinical genetics service that is staffed by a multidisciplinary team of genetics and oncology clinicians. Therefore, the effectiveness and implementation evidence generated from this real-world health service setting aims to optimise the relevance of the outcomes of this trial to the practice of genetic counselling while enhancing the operationalisation of the screening tool in routine practice.

**Trial registration:**

Australian New Zealand Clinical Trials Registry registration number 12621001582842p. Date of registration: 19th November 2021.

**Supplementary Information:**

The online version contains supplementary material available at 10.1186/s13063-023-07723-0.

## Background

Genetic counselling and testing for cancer predisposition syndromes are increasingly being offered to individuals with and without cancer diagnoses due to the evidence of improved health outcomes for those identified with a germline pathogenic variant (PV) [1, 2]. Individuals without cancer who are aware they have inherited a cancer-causing germline PV have the opportunity to engage in efficacious cancer risk management strategies demonstrated to reduce cancer-related morbidity and mortality [3, 4]. For those with cancer, the diagnosis of a germline variant offers treatment options [5, 6], refines prognosis, and defines future cancer risks with associated risk management strategies. The genetic counselling process facilitates informed decision-making about genetic testing and any subsequent risk management options [7], and promotes patient empowerment and adaption to genetic status after receipt of results [8, 9].

Gold standard genetic counselling is patient-centred, with patient needs identified and addressed by skilled practitioners. The genetic counselling process facilitates informed decision-making about genetic testing, supports empowerment and adaptation to genetic information, and promotes communication of genetic information to at-risk family members [8, 10–13]. The provision of genetic counselling by the multidisciplinary teams staffing cancer-specific clinical genetics services (Familial Cancer Centres), increasing demand upon the limited genetic counsellor workforce [14], and the increasing provision of genetic testing by medical practitioners who work externally to these clinical genetics services mean that the provision of genetic counselling may vary in quality and quantity [15]. Therefore, transformative approaches to genetic counselling practice are required to ensure consistent, patient-centred care prevails [16, 17].

Screening tools, often used in other healthcare settings to efficiently identify patient needs, may facilitate genetic counselling and support patient-centred care. Deployment of patient screening tools in clinical oncology settings is becoming routine, yet examples of routine use in clinical genetics services have not been published. This is despite the existence of specifically developed and validated psychosocial screening tools for use in clinical genetics [18, 19]. The Genetic Psychosocial Risk Instrument (GPRI) is a validated genetics-specific screening tool designed to identify psychological risk factors that predict distress in patients undergoing genetic testing [19].

The GPRI was piloted with patients and clinicians (genetic counsellors, clinical geneticists, and medical oncologists) in the Parkville Familial Cancer Centre (PFCC), in Victoria, Australia, from December 2018 to March 2019 and it was determined that this screening tool was acceptable and feasible to patients and clinicians, and useful for clinicians during appointments [20]. While the rigorous development and validation of the GPRI together with the demonstrated acceptability, feasibility, and usefulness make this an ideal genetic counselling intervention, the GPRI has not been evaluated regarding its effectiveness in improving patient outcomes or whether it can be implemented routinely into practice. Therefore, the objective of this study is to test the use of the GPRI and examine the implementation of this screening tool in a clinical genetics service providing cancer genetic counselling.

## Methods

This study is sponsored by the Peter MacCallum Cancer Centre and was approved by the Peter MacCallum Human Research Ethics Committee (HREC/78093/PMCC-2021) on 22 December 2021. Site governance authorisation was granted on 7 February 2022 for the Peter MacCallum Cancer Centre and on 7 October 2022 for the Royal Melbourne Hospital, with a Clinical Trial Research Agreement executed between the sponsor and Melbourne Health. Trial oversight is undertaken by a steering committee comprised of the investigator team (authors [name]) and two consumer representatives and meets six monthly. The principal investigator ([name]) is responsible for leading the trial, including monitoring enrolment, training of study staff, and providing education sessions to clinicians prior to signing the delegation log. Data management and quality is monitored by co-investigator and biostatistician ([name]), which is presented at the six monthly steering committee meetings. Further, the forced choice and required field options in the REDCap database are used throughout to minimise missing data or invalid responses.

### Research aims

This hybrid type II effectiveness-implementation randomised clinical trial includes two aims:Assess the effectiveness of using the GPRI, relative to usual care, in improving patient outcomes including empowerment (primary outcome) after genetic counselling and testing for an inherited cancer predisposition; andAssess the implementation of the GPRI in genetic counselling appointments in terms of adoption, cost-effectiveness, fidelity, feasibility of routine use, penetration, and sustainability.

### Setting

This research will be conducted at the PFCC, the conjoint clinical genetics service at the Peter MacCallum Cancer Centre and the Royal Melbourne Hospital, located in Victoria, Australia. Patients are referred to the PFCC for a risk assessment based on personal and/or family history of cancer. Referrals are actioned by an intake assistant, with genetic counsellor oversight, who contacts the patient to obtain additional family history and/or clinical information. Once the intake process is complete, an appointment is booked with up to 6 weeks wait for the appointment date. Patients who are deemed at increased risk of an inherited predisposition to cancer and are likely to be offered genetic testing will typically attend two appointments: (1) a pre-test appointment during which consent for genetic testing is discussed and obtained; and (2) a results appointment at which the genetic test result is disclosed. The clinic is staffed by clinicians, comprising genetic counsellors, clinical geneticists, medical oncologists, gastroenterologists, and clinical genetics fellows.

### Study design

A hybrid type 2 effectiveness-implementation trial has been designed to assess the effectiveness of using the GPRI in PFCC appointments while also assessing the implementation strategy (Table 1) [21].

**Table 1 Tab1:** Hybrid effectiveness-implementation trial map

	**Aims**	**Framework**	**Constructs**	**Outcome**	**Analysis level**	**Measurement**	**Data collection**
**Effectiveness**	To assess the effectiveness of using the GPRI in genetic counselling	FOCUS-GC	Communication strategy	Identify patient psychosocial needs during appointment	Clinician	No. of patient needs identified	Appt. checklist, audio recording
				Address patient psychosocial needs during appointment	Clinician	Y/N patient needs address	
			Process measures	Appointment length	Service	Time (minutes)	Appt. checklist, audio recording
				Referrals for support	Clinician	No. & type of referrals offered	Appt. audio recording
						No. & type of referrals made	Clinical data
				Letters to at-risk relatives	Clinician	No. letters written	Clinical data
			Patient care experiences	Satisfaction with appointment	Patient	Genetic Counselling Satisfaction Scale	t3 & t6
			Patient changes	Empowerment	Patient	Genetic counselling Outcome Scale	−t1, t3 & t6
			Patient health	Distress	Patient	Multidimensional Impact of Cancer Assessment Questionnaire	t6
				Adaption	Patient	Psychological Adaption Scale	t6 & t7
				Cancer risk management	Patient	Uptake of strategies	t7
			Family changes	Communication to at-risk relatives	Patient	No. of family members informed	t7
**Implementation**	To assess the implementation of the GPRI in genetic counselling	Implementation Outcomes Framework	Acceptability	Acceptable to implement GPRI in genetic counselling appointments.	Patient	Acceptability patient survey	Complete
					Clinician	Acceptability staff survey	
			Adoption	Uptake by patient	Patient	GPRI pilot (early stage)	Complete (uptake 94%)
				Uptake by clinician	Clinician	Use by clinician (Y/N)	Appt. audio recording
			Feasibility	Feasible to implement GPRI in genetic counselling	Patient	Feasibility patient survey	Complete
					Clinician	Feasibility staff survey	Complete
						Feasibility of using GRPI routinely	Structured interviews
			Fidelity	GPRI implemented as intended	Clinician	Use by clinician (Y/N) and extent of use	Appt. checklist, audio recording
			Implementation cost	Health resource use	Service	Cost to service ($AUD)	Health economic data
			Penetration	Integration of GPRI in genetic counselling appointments	Clinician	No. of clinicians who use GPRI	Appt. checklist, audio recording
			Sustainability	Intention to routinely use GPRI	Clinician	Sustainability of using GPRI routinely	Structured interviews

The effectiveness of the GPRI will be tested using a superiority randomised control trial (RCT) to assess outcomes of using the GPRI during PFCC appointments and will be guided by the Framework for Outcomes of Clinical commUnication Services for Genetic Counselling (FOCUS-GC) [22]. This trial uses a parallel group design where participants will be randomised to the control group (no GPRI) or the intervention group (GPRI). Patients in the control group will receive usual care consisting of the current standard of genetic counselling where the GPRI is not used. Implementation of the GPRI will be concurrently assessed guided by Proctor’s Implementation Outcomes Framework [23]. Given the acceptability and feasibility were assessed during the pilot [20], the remaining outcomes, cost-effectiveness, adoption, feasibility of routine use, fidelity, penetration, and sustainability, will be assessed during this hybrid trial from the perspective of clinicians and the healthcare service.

#### Intervention

The GPRI is a 20-item instrument demonstrated to have high reliability (Cronbach’s alpha at 0.81), construct validity that highly correlates with other relevant psychometric scales, and a predictive value of 0.78 [19]. This tool consists of three subscales: (1) personal and family history of inherited condition; (2) perceived impact and personal adjustment to genetic testing; and (3) history of mental health concerns [19]. Nineteen of the items are summed to determine a GPRI score (range 10–100) and the scale has a clinically meaningful cutoff score of 50, which identifies 84% of patients who are at increased risk of distress after they receive their genetic test results [19]. The remaining item is used to indicate whether further counselling is needed after the genetics appointment.

Participants who are randomised into the intervention group will be emailed a link to the GPRI hosted on REDCap 3 days prior to both PFCC appointments and participants will complete the GPRI online prior to this appointment. The GPRI score is calculated using the REDCap auto-scoring capability and the completed measure and score is emailed to the relevant clinician. Given this is a low-risk intervention and the intervention involves completion of a validated screening tool, there will be no modification to the intervention. Participants in the intervention group who have not completed the GPRI within 24 h of their appointment are sent a reminder SMS that includes the URL to the online GPRI. Those who subsequently do not complete the GPRI receive usual care of standard genetic counselling and will continue in the trial for all follow-up assessments scheduled.

#### Primary outcome

The primary outcome of patient empowerment, as measured by the Genetic Counselling Outcome Scale (GCOS-24), is measured from baseline to the primary timepoint of 2 weeks after the second PFCC appointment. The GCOS-24 is validated to measure change in patient empowerment from pre- to post-genetic counselling and consists of 24 items each with a 7-point Likert scale response option scored from 1 “strongly disagree” to 7 “strongly agree” [24]. Negatively worded responses options are transformed so that all increases in scores represent an increase in empowerment and the total score is calculated by determining the sum of the scores [24].

#### Secondary outcomes

The effectiveness of using the GPRI, relative to usual care, will be further explored through secondary outcomes including change in GCOS-24 score from baseline to 2 weeks after the first PFCC appointment and proportion of respondents who meet the Minimum Clinically Important Difference (MCID) whose GCOS-24 score changes ≥10 points from baseline to 2 weeks after the second PFCC appointment [25]. Other secondary outcomes include patient satisfaction at 2 weeks after first and second PFCC appointments, patient adaptation 2 weeks and 6 months after the second PFCC appointment, and impact of genetic test result 2 weeks after the second PFCC appointment. Uptake of cancer risk management strategies and communication of genetic information to at-risk family members will be assessed at 6 months after the second PFCC appointment. The proportion of psychosocial needs identified by clinicians during the PFCC appointments, support offered after the PFCC appointments, and duration of the PFCC appointments will be established. Implementation outcomes including cost-effectiveness, adoption (uptake of the GPRI by clinicians during appointments), fidelity (use of GPRI and extent of use by clinicians during appointments), penetration (number of clinicians who use the GPRI during appointments), and clinicians’ perceptions of the feasibility and sustainability of using the GPRI routinely will also be assessed.

### Participants

#### Patients

This study will invite patients who are at increased risk of an inherited predisposition to cancer and are attending the PFCC for genetic testing. Patients attending their first appointment and who are likely to be offered genetic testing will be eligible. Involvement in this research is voluntary.

##### Eligibility

Patients will be considered eligible once their intake process is complete and their PFCC appointment has been booked. Inclusion in the study will be assessed by the research team, with input from the clinical team, based on the following criteria:Aged 18 years or older;Literate in English;Reasonable internet access and capacity to complete computer-based surveys; andLikely to be offered a genetic test during their first appointment.

Patients will be excluded if they have a known cognitive impairment or are eligible for the PRiMo study (using Polygenic Risk Modification to improve breast cancer prevention; HREC no. HREC/64060/PMCC; ANZCTR: ACTRN12621000009819). Patients will become ineligible to participate if they do not consent to genetic testing during their first appointment.

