### Statistical analysis

The biostatistician will devise a formal detailed statistical analysis plan for the study prior to unblinding. The analysis set will consist of all participants who were randomised, with all participants reported and analysed according to their randomised study arm. There is no interim-analysis planned due to the low risk of harm to participants presented by this trial.

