#### Primary outcome

Primary outcome GCOS-24 scores will be analysed using a constrained longitudinal data analysis (cLDA) [32] model assuming a common mean across groups at baseline and a different mean for each group at each follow-up time point. The response will consist of all GCOS-24 scores (scores at baseline, and at 2 weeks after the first PFCC appointment and 2 weeks after the second PFCC appointment) and the model will include a random intercept for clinician and an unstructured variance-covariance matrix for the individual’s repeated measurements, factors representing treatment, time (categorical), and treatment-by-time interaction, and the stratification factors sex and cancer status at baseline, and will be further adjusted for cancer type. The mean change in GCOS-24 scores from baseline to each follow-up time point between the intervention group compared to the control group will be obtained. The primary hypothesis will be evaluated by obtaining the estimated difference between intervention and control groups in mean change in GCOS-24 score from baseline to 2 weeks after the second PFCC appointment, a two-sided 95% confidence interval and a *p*-value. This model provides valid inference in the presence of missing data if the data are missing at random. An analysis will be conducted using the delta-adjustment method under the pattern-mixture modelling framework in the context of multiple imputation to assess sensitivity to missingness not at random.

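### Randomised participants who decline genetic testing at the first appointment become ineligible, and this withdrawal rule is not reconciled with the all-randomised analysis set

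*Protocol article*

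**What the plan says.** All references are to the protocol article.

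- **Eligibility:** patients are judged eligible once the appointment is booked, partly on being likely to be offered a test. Then: "Patients will become ineligible to participate if they do not consent to genetic testing during their first appointment".
- **Intervention:** those "randomised into the intervention group will be emailed a link to the GPRI hosted on REDCap 3 days prior to both PFCC appointments".
- **Setting:** the first visit is "a pre-test appointment during which consent for genetic testing is discussed and obtained". The second is the visit at which the result is disclosed.
- **Primary outcome (Methods):** empowerment on the GCOS-24 "is measured from baseline to the primary timepoint of 2 weeks after the second PFCC appointment".
- **Statistical analysis:** "The analysis set will consist of all participants who were randomised, with all participants reported and analysed according to their randomised study arm".
- **Primary outcome (Data analysis):** the cLDA response includes the baseline score and both follow-up scores. Of missing data it says: "This model provides valid inference in the presence of missing data if the data are missing at random". A delta-adjusted multiple-imputation analysis is planned for missingness not at random.
- **Randomisation:** patients and clinicians are not blinded.

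The only continuation rule stated is for intervention patients who do not complete the GPRI; they "will continue in the trial for all follow-up assessments scheduled". Nothing comparable is stated for patients who decline testing.

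**The concern.** A rule that ends participation after randomisation is harmless only if the event that triggers it is unrelated to the arm. Here the trigger is a decision made in the consultation that the GPRI is meant to change. The Background says that genetic counselling supports informed decisions about testing, and one GPRI subscale covers the perceived impact of, and adjustment to, testing. Only the intervention arm has the tool, and everyone in the consultation knows the allocation. The number or kind of patients who decline could therefore differ between arms.

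If it does, the follow-up scores compare selected groups rather than the groups formed by randomisation. A considered decision not to be tested could also reflect empowerment, and the trial would not measure it. The analysis plan cannot repair this later, because a questionnaire that was never sent cannot be recovered.

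**Working it through.** **Step 1: order of events.** The article does not give the exact moment of randomisation, but its order follows from the text.

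1. Appointment booked and eligibility judged (Eligibility).
2. Randomisation. It must fall before the next step, because the GPRI link is sent only to patients already allocated to the intervention.
3. GPRI link sent 3 days before the first appointment (Intervention; t1 in the Fig. 1 legend).
4. First appointment: testing discussed and consent sought (Setting; t2).
5. Decliners become ineligible (Eligibility).
6. GCOS-24 2 weeks after the first appointment (t3) and 2 weeks after the second (t6).

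The rule at step 5 follows randomisation in both arms, and follows exposure to the GPRI in one.

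**Step 2: Eligibility against Statistical analysis.** One section ends participation; the other keeps everyone randomised in the analysis set. Both can be met only if decliners stay in the cLDA with a baseline score and no later ones. The article does not say that this is intended. Under that reading the model in effect fills in decliners' later scores from participants in the same arm with observed scores, using baseline. The Sample size section assumes, as a conservative choice, zero correlation between baseline and later scores. At zero correlation the baseline score corrects nothing; with positive correlation it corrects part.

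**Step 3: size of the possible bias.** Let qI and qC be the decline rates in the intervention and control arms, and D the amount by which decliners would score below the others, the same in both arms. Assume no true effect over all randomised patients. In each arm the mean of those who remain exceeds the all-randomised mean by q × D, so losing decliners shifts the contrast by

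bias = (qI − qC) × D.

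The standard error at the planned evaluable size is 20 × √(2/86) = 3.05, using the plan's SD of 20 and 86 per arm (step 4). All rates and gaps below are assumptions; the documents give none.

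| qC | qI | D (units) | Bias (units) | Share of the 10-unit target | Two-sided type I error |
|---|---|---|---|---|---|
| 5% | 5% | any | 0 | 0% | 5.0% |
| 5% | 10% | 10 | 0.5 | 5% | 5.3% |
| 5% | 10% | 20 | 1.0 | 10% | 6.2% |
| 5% | 15% | 20 | 2.0 | 20% | 10.1% |

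A gap of 20 units is one full SD, so the last two rows are demanding cases. If decliners would score higher than the others, the sign reverses.

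**Step 4: power, for completeness.** The plan's 246 reproduces. For a difference of 10, SD 20, two-sided 5% and 90% power, the t-based calculation gives 86 per arm; 86/0.7 = 122.9, so 123 per arm and 246 in total. The 30% attrition is thus already inside 246. If recruitment stops at 246 and decliners are lost on top of that attrition, 123 × 0.7 × (1 − q) per arm remain. By the normal approximation power is 90.7% at q = 0, 89.2% at 5%, 87.5% at 10% and 85.6% at 15%. Both conditions are open. The Recruitment section's 702 invitations at 50% uptake imply 351 consenting, or 175.5 per arm. If all were randomised, 15% declining would leave 175.5 × 0.7 × 0.85 = 104.4 per arm and power of about 95%.

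**The case against.** The rule has a rationale. The trial's aim concerns outcomes after counselling and testing, and the primary timepoint is tied to a results appointment that a decliner would not be expected to have. For such patients the primary endpoint is undefined rather than merely uncollected. How to handle that is an estimand choice, which a condensed article may leave to the full protocol or the analysis plan. This stands, and it is why the fix does not impose one treatment of the primary timepoint.

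Three stronger conclusions are tempting, and the documents do not support them.

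- *A reader might infer that decliners' data are deleted and that the two rules cannot both be followed.* The Eligibility rule governs participation and says nothing about removing data. A decliner can stop participating and still count in the all-randomised set through the baseline score, with the missing-at-random model and the delta-adjusted analysis applied to the rest. What remains is that the article does not say so, and that follow-up would still stop.
- *A reader might infer that the primary comparison is biased.* That needs decline rates, or the kind of patient who declines, to differ by arm. An effect of the GPRI on test uptake is plausible but nowhere stated, and patients are selected as likely to be offered a test.
- *A reader might infer that the trial loses power.* That holds only if recruitment stops at 246 and the 30% attrition does not already cover decliners. The documents settle neither.

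**Conclusion.** The concern holds as a withdrawal rule that acts after randomisation, on a decision the intervention could influence, and that is not reconciled with the all-randomised analysis set. The sequence is established from the text; the bias is possible, not shown. Under the assumed inputs it ranges from zero (equal decline rates and similar decliners) through 0.5 units (5-point rate difference, 10-unit gap) to 2 units (10-point difference, 20-unit gap), the last being a fifth of the target difference. These figures assume the same gap in both arms and no recovery of the lost scores through baseline. The planned missing-data analyses can help only if decliners stay in the dataset, and they work better the more of the decliners' scores are observed. No claim about power is made.

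**What to change.** 1. Amend the Eligibility rule so that it does not remove anyone already randomised, and state that participants who decline testing remain in the all-randomised analysis set.
2. Send decliners the GCOS-24 already scheduled 2 weeks after the first appointment, and include it with the baseline score in the primary cLDA. This needs no new endpoint.
3. Report the number declining testing by arm.
4. State how declining is handled at the primary timepoint. One route is to treat the score as missing, with the planned delta-adjusted sensitivity analysis. Another, optional, is a GCOS-24 at a date matched to the usual interval, labelled as taken without result disclosure. Pooling such scores in the primary model changes the estimand, so it should be a stated choice.
5. Label any comparison restricted to tested participants as supplementary.

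The cost is a protocol amendment and a few extra automated questionnaires. Clinical care does not change.
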